### Ethics Approval and Consent to Participate.

Full Health Research Authority (HRA) and NHS Research Ethics Committee (REC) approval has been granted (IRAS ID: 314923; 22/LO/0318).

### Randomisation

Randomisation lists created by an independent statistician prior to recruitment to the study, and they will be delivered to the recruitment sites by sealed envelope method. All participants and study staff will not be blinded apart from the principal statistician [RG] who will be unblinded at the end of the study after data lock has occurred.

Unblinded results will be discussed in closed sessions from which the trial statistician will be excluded. Unblinded interim results will be generated (if necessary) by the independent statistician and made available to the IDMEC for each sitting if requested by the Chair of the committee.

### Analyses

We will seek evidence of the feasibility of conducting a larger subsequent RCT by examining the following parameters:

- Power calculation: We will determine the pooled standard deviation for the baseline score of the primary outcome variable, as well as the correlation of the primary outcome at baseline and at follow-up (T3). These data, along with the mean clinically important difference (MCID), will be used in the sample size calculation for a fully powered subsequent study.
- Recruitment: Number of referrals from each source, numbers ineligible, reasons for ineligibility, rates, and reasons for refusal to be included in the study.
- Randomisation: whether groups are balanced and randomisation possible in this environment.
- Withdrawals: Attrition rates and reasons for withdrawing throughout the study, follow-up rates.

Additionally, to fulfil the secondary objectives, descriptive analyses will be performed on the following outcomes: resources needed to complete CBT-f-DDD; health economics evaluation; therapist adherence to CBT-f-DDD; sample characteristics; and acceptability outcomes.

Qualitative data from interviews with therapists and participants will be transcribed and analysed using thematic analysis within NVivo software (supervised by co-applicant [name]). This will be guided by Braun & Clarke’s six stage process (42), and conducted collaboratively to include the perspectives of clinicians and those with lived experience within the research team. Interviews will be recorded using an encrypted device for the audio recording, and data will be stored securely within the NHS. Transcription of this audio recording will be done by a professional external agency which has an over-arching contract with UCL that covers all GDPR issues (as outlined in the collaboration agreement between UCL and C&I). These audio files will be destroyed at the end of the project.

As well as providing an in-depth exploration of treatment experiences and perceived impacts (from both provider and recipient perspectives), analysis will be structured to produce clear summaries of feasibility and acceptability issues as reported by therapists and participants. These analyses will inform therapy and trial process modifications in advance of any subsequent definitive trial.

The final dataset will only be accessible to the minimum number of individuals necessary for quality control, audit, and analysis, which will be members of the research team and potentially members of the TSC and IDMEC. Given these data could have the potential for reverse deanonymisation of participants, the final study dataset will not be available to others beyond the immediate research team and committees. However, the details of the statistical analysis and the analysis of transcripts will be made more widely available.

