## Abstract

Background: Depersonalisation-Derealisation Disorder (DDD) is a distressing mental health condition which causes individuals to have a sense of ‘unreality’ or detachment about themselves and/or the world around them. DDD is chronically under-researched, and as a result, under-diagnosed, with a population prevalence of about 1%. In systematic reviews, Cognitive Behavioural Therapy (CBT) has been found to be the only intervention with significant clinical impact on alleviating the symptoms of DDD. However, previous studies have suffered from small sample sizes, reliance on expert clinicians to provide therapy and narrow population demographics. This feasibility randomised controlled trial aims to provide more robust evidence for the treatment efficacy of CBT in DDD.

**Methods**: The study aims to recruit 40 participants from two NHS trusts, 20 per arm from two community Mental Health NHS services in London. The intervention group will receive 12-24 individual CBT sessions over a 6-month period from CBT therapists following specialist training for DDD. The control group will receive Treatment as Usual. We will assess the feasibility of a future RCT through measuring the acceptability of the intervention, and assessing our ability to recruit, retain and randomise participants. We will calculate the correlation of scores on the Cambridge Depersonalisation Scale, its baseline standard deviation, assess the magnitude/direction of change and characterise the uncertainty in the outcome scores and the probability that the results have been obtained by chance.

**Discussion**: The outputs of this trial will guide whether a definite RCT is feasible and acceptable, for both the clinician and participant.

Trial Registration: The ISRCTN registration number is ISRCTN97686121(<https://doi.org/10.1186/ISRCTN97686121>).

Keywords: CBT, Derealization, Depersonalization, NHS, Trial, Feasibility

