### Participants

The study will aim to recruit 40 participants, 20 participants in each arm. All participants will be aged between 16-75, living in London, and have symptoms of Depersonalisation and/or Derealisation currently meeting DSM-V (1) criteria for DDD. This will be assessed by the research assistant (RA) in their initial (T0) screening interview by asking the participant the following two questions, which make up part of the diagnostic criteria in the DSM-V (1) :

“Over the last two weeks, how often have you had:

1. Experiences of unreality, detachment, or being an outside observer with respect to one's thoughts, feelings, sensations, body, or actions (e.g., perceptual alterations, distorted sense of time, unreal or absent self, emotional and/or physical numbing). [Depersonalisation]

0 =not at all; 1=several days; 2=more than half the days; 3=nearly every day”

1. Experiences of unreality or detachment with respect to surroundings (e.g., individuals or objects are experienced as unreal, dreamlike, foggy, lifeless, or visually distorted). [Derealisation]

0=not at all; 1=several days; 2=more than half the days; 3=nearly every day.”

The total score will be calculated as follows:

1. Total score = (a + b).
   1. Scores <3 = mild-moderate DDD.
   2. Scores >=3 = moderate-severe DDD.

Other DSM-V criteria will be assessed including intact reality testing, that the symptoms result in significant distress and/or functional impairment, and that the DDD symptoms cannot be better explained by another condition. Participants will be excluded if they have any of the following co-morbid diagnoses: any psychosis spectrum disorder, substance dependence, intellectual disability, Post Traumatic Stress Disorder (PTSD), or cognitive impairment due to head injury or organic disorder. Comorbidity with anxiety and/or depressive disorders will not be an exclusion criterion.

Additionally, participants will be excluded from the study if they have previously received CBT specifically for the treatment of DDD; have a score below clinical severity (i.e. total score < 3) on the diagnostic questions; cannot provide informed consent; do not have sufficient proficiency in English to engage in CBT; require special communication needs arrangements; are not registered with a GP practice or are involved in any other mental or physical research studies (including drug trials).

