### Sample Size

There is no formal sample size calculation, or priori power calculation. Instead, a minimum of 24 participants, 12 in each arm, has been suggested for pilot studies (26). This minimum recruitment strategy requires recruiting 29 eligible participants in total (encompassing a nominal 20% dropout rate). This study aims to recruit 20 participants in each arm who complete. We believe this number will give us a final sample large (and sufficiently diverse) enough to assess the practicalities of recruitment, retention, randomisation, and intervention delivery, as well as to obtain the necessary data for the statistical inferences required.

A previous naturalistic self-controlled cross-over study found the effect size between the treatment period and the waiting period to be 0.52 (improvement in favour of treatment). This translated into a decrease of 36 points on the CDS Scale. Using this change score, a correlation of 0.9 which was observed for intra-participant correlation, and the standard deviation of the CDS at each phase of the crossover study, we anticipated that the required sample size would be 29 participants per arm (using the ANCOVA method). Our planned recruitment of 20 per arm provides sufficient power to provide information on the magnitude, direction, and precision of the treatment effect from the feasibility study to power (with sufficient precision) a subsequent definitive RCT if appropriate (15).

To meet our relatively conservative aim of 20 participants completing the trial in each arm we will need a recruitment rate of 5-10 participants a month during the 6-month recruitment period. Historical data demonstrates a referral rate of one referral per week, which would be adequate for the proposed sample size.

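### The protocol sets no progression criteria for its feasibility question, and its recruitment figures do not agree with one another

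*Protocol*

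**What the plan says.** The Abstract states the purpose: "The outputs of this trial will guide whether a definite RCT is feasible and acceptable". The Analyses section gives the procedure: "We will seek evidence of the feasibility of conducting a larger subsequent RCT by examining the following parameters". The items that follow are the inputs for a later power calculation, referral and refusal counts, whether the groups are balanced, and attrition and follow-up rates. None has a target, an acceptable level or a rule for what follows from it, and no such rule appears elsewhere in the protocol.

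The recruitment figures are these:

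- Participants: "The study will aim to recruit 40 participants, 20 participants in each arm".
- Sample Size, the aim: "This study aims to recruit 20 participants in each arm who complete".
- Sample Size, a floor: "a minimum of 24 participants, 12 in each arm, has been suggested for pilot studies", followed by "This minimum recruitment strategy requires recruiting 29 eligible participants in total (encompassing a nominal 20% dropout rate".
- Sample Size, the pace said to be required for 20 completers per arm: "we will need a recruitment rate of 5-10 participants a month during the 6-month recruitment period".
- Sample Size, the supply: "Historical data demonstrates a referral rate of one referral per week, which would be adequate for the proposed sample size".

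**The concern.** The main product of a feasibility trial is a judgement on whether to go ahead. If the protocol does not say what would count as enough recruitment, retention or session uptake, that judgement is made after the results are known.

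A reader would look to the planning figures for an implied yardstick. Two pairs of them are inconsistent: 40 recruited against 40 completing, and one referral a week against 5-10 recruits a month. Someone reading the final report could then call a mid-range result a success or a shortfall, depending on which figure is cited.

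**Working it through.** **Inputs, all from the protocol.** 40 recruited (Participants). From Sample Size: 40 completing (20 per arm), minimum 24 completing, 29 to recruit for that minimum, 20% dropout, 5-10 recruits a month for 6 months, and one referral a week. Six months is taken as 26 weeks, so one a week is 52/12 = 4.33 a month.

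**1. The protocol's own figure.** 24 × 1.2 = 28.8, rounded up to 29, so the stated number is reproduced. Multiplying by 1.2 does not allow fully for a 20% loss: 29 × 0.8 = 23.2 completers, just under 24. Dividing by the retained fraction gives 24/0.8 = 30.

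**2. Recruited against completed.**

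- 40 recruited: 40 × 0.8 = 32 completers, or 16 per arm.
- 40 completers: 40/0.8 = 50 recruited, or 25 per arm. The multiplication behind the 29 gives 40 × 1.2 = 48.
- By either method, 40 cannot be both the number recruited and the number completing at 20% dropout.

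**3. Monthly rate.**

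- 5 × 6 = 30 recruited, and 30 × 0.8 = 24 completers.
- 10 × 6 = 60 recruited, and 60 × 0.8 = 48 completers.
- 40 completers needs 50/6 = 8.3 a month (48/6 = 8.0 by the multiplication method).
- The lower end of the stated range delivers the minimum of 24, not the 40 completers for which the rate is said to be needed.

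**4. Referral supply.** One a week for 26 weeks is 26 referrals. Suppose every one is eligible and consents:

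| Recruits needed | Months at 4.33 a month | Share of 26 referrals needed |
|---|---|---|
| 29 | 6.7 | 112% |
| 30 | 6.9 | 115% |
| 40 | 9.2 | 154% |
| 50 | 11.5 | 192% |

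All four exceed what the stated supply provides in 6 months.

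**5. A mid-range result.** Take 30 recruited and 24 completing.

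| Figure | Result |
|---|---|
| Minimum of 29 recruited | met |
| Minimum of 24 completing | met |
| 5 a month (30/6 = 5.0) | met |
| 40 recruited | 30/40 = 75%, short by 25% |
| 40 completing | 24/40 = 60%, short by 40% |

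**6. Precision.** If 40 are recruited and 32 retained (80%), the exact 95% CI is 64% to 91%. A retention threshold chosen after seeing that result could sit on either side of it with little to contradict the choice.

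**The case against.** The strongest reply has four parts.

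**Criteria may sit elsewhere.** The statistical analysis plan is not to hand, and the TSC could hold progression rules. This stands as far as it goes: the absence of thresholds from the protocol does not prove that none exist. It does not rescue the recruitment figures, which conflict within the protocol. A threshold written elsewhere would still have to choose between them.

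**Most of the figures have different jobs.** A reader might infer that 24 or 29 contradicts 40. It does not, because a floor below a target is normal practice. Nor does the Analyses section say that its measures will be judged against the Sample Size figures; they are simply the only yardsticks the protocol offers. The conflicts that remain are recruited against completed, and referral supply against recruitment rate.

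**The consequence can be overstated.** A reader might infer that the trial cannot answer its question, or that any result would support either conclusion. The protocol does not support that. It says the outputs will guide the decision, and the recruitment, retention, correlation and standard deviation results will be reported whatever happens. Twenty recruits would fail every recruitment figure, and 50 recruits with 40 completers would meet them all. The ambiguity lies between such extremes.

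**Historical referrals may not be the whole supply.** The protocol also plans website advertising and self-referral, and does not say whether one a week is a total or a rate per trust. If it were per trust (an assumption), two trusts would give 52 referrals in 26 weeks. Reaching 40 would then need 40/52 = 77% of referrals to be randomised, and 50 would need 50/52 = 96%, before any exclusion or refusal. The protocol claims adequacy from the referral rate alone and gives no conversion rate.

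**Conclusion.** The point holds in this form. The protocol states no progression criteria for its main question, and its recruitment aim is given in two incompatible ways that differ by 10 recruits (40 against 50) or 8 completers (32 against 40). The lower end of the stated monthly rate reaches 24 of the 40 intended completers. Read as a total, the stated referral rate gives 26 people in 6 months, so describing it as adequate is wrong even for the minimum of 29.

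The figures rest on the protocol's nominal 20% dropout applied equally to both arms, a 26-week recruitment window, and the referral rate being a total across sites. The size of the supply gap depends on the last of these; the recruited-against-completed conflict does not. The practical effect is confined to mid-range results. On the protocol's own referral figure a result below target is a realistic prospect, so the matter should be settled in advance.

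**What to change.** 1. **State once what 40 means.** Either 40 recruited, with about 32 completers expected, or 40 completing, with 50 to recruit. Correct the minimum to recruit from 29 to 30 (24/0.8). Restate the monthly rate to match: 40/6 = 6.7 or 50/6 = 8.3 a month.
2. **Correct or remove the adequacy statement.** For example, restate the recruitment window (about 9 months for 40 at one referral a week, even at full uptake) or the number expected within 6 months. If other sources are counted on, say how many recruits they should add.
3. **Fix one stop/amend/go rule.** Before recruitment data are reviewed, the TSC should agree a rule covering recruitment, retention at T3 and the proportion of the CBT arm reaching the protocol's minimum number of sessions. Recruitment and retention should be set jointly, so that go delivers the target chosen in step 1 and amend never falls below 24 completers. Separate cut-offs can fail this test: 29 recruited with 60% retained leaves 29 × 0.6 = 17.4 completers. Report each measure with an exact 95% CI.

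The cost is protocol wording and one TSC decision, with no further data collection. If the sponsor chooses 40 completing, recruiting 50 means 10 more participants than Participants now states; that follows from the aim already in Sample Size. The downside is that the sponsor commits in advance to a result that may read as amend.

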### Adverse Events

This is not a high-risk study and we do not anticipate any serious adverse events occurring within the study. However, we have undertaken a Research Risk Assessment and a Data Protection Impact Assessment to identify potential risks to mitigate against these as much as possible in advance. From this a Risk Management Plan was put in place to inform RAs of the appropriate procedure when/if there is a disclosure of suicidal ideation made. Finally, we are aware that within any therapy there is the potential discussion of past difficult events which may cause distress to the participant. All interventions will be carried out by qualified and trained NHS clinicians who will also receive regular, specialised supervision by ECMH.

## Discussion

This paper presents the protocol for a feasibility study investigating a cognitive behavioural therapy intervention for individuals with DDD. This research came about after two clinical audits from a national specialist NHS service indicated that CBT adapted for DDD might be of benefit. However, these were small scale, from a specialist service and participants had not been randomised, so the next step in both research and treatment provision in this clinical population was to identify whether a future RCT is feasible and whether the intervention, CBT-f-DDD, is acceptable to both clinicians and clients. The findings of the feasibility study will aid in establishing the key parameters for a future RCT trial (if appropriate). Additionally, this feasibility paper will also help in dissemination of information about CBT-f-DDD for up to 20 clinicians, hopefully increasing awareness and improving accuracy in diagnoses of DDD for both NHS trusts involved.

Protocol version: V6.6 September 2023

## List of Abbreviations

BEH, Barnet, Enfield and Haringey; CBT cognitive behavioural therapy; CBT-f-DDD, Cognitive Behavioural Therapy for Depersonalisation Derealisation Disorder; CCG, Clinical Commissioning Group; CDS, Cambridge Depersonalisation Scale; CI, Chief Investigator; CIS-R, Clinical Interview Schedule-Revised; CTS-R, Cognitive Therapy Scale-Revised; C&I Camden and Islington; DDD, Depersonalisation Derealisation disorder; DES, Dissociative Experiences Scale; GAD-7, Generalised Anxiety Disorder Assessment 7; IDMEC, Independent Data Monitoring and Ethics Committee; NHS, National Health Service; PAG, Patient Advisory Group; PHQ-9, Patient health questionnaire 9; RA, Research Assistant; SSRI, Selective Serotonin Reuptake Inhibitor; TAU, Treatment as Usual; TMG, Trial Management Group; TSC, Trial Steering Committee; UCL, University College London; WSAS, Work and Social Adjustment Scale

## Declarations

## *Acknowledgements*

We acknowledge the funder of the study (NIHR) and the generous participation of the patients who have agreed to take part in this study.

Appendix A

**Table A1.** Spirit Figure

Appendix B

**Figure B1.** Adapted CBT-f-DDD checklist.
